#### Warm water immersion (thermoneutral control)

3.4.3

Because hydrostatic effects of water immersion may affect physiology, we include a comparison group comprised of individuals exposed to warm water immersion (thermoneutral condition). We follow procedures identical to the heat therapy protocol, except that the warm water therapy bath will be 36 °C. Prior work has shown that these conditions maintain core temperature within 0.2 °C of resting (3). This will ensure that both groups are exposed to conditions that are equivalent in terms of any hydrostatic effects, engagement, and patient experience.

### Participant engagement

3.5

Participants are encouraged to attend all assigned sessions. Participants receive renumeration upon completion of the baseline study visits, as well as renumeration for the intervention visits. In addition, upon enrollment participants receive a small welcome package containing items relevant to the intervention that may improve their experience (i.e., towel, insulated water bottle, wet/dry bag, etc).

### Blood processing

3.6

At the baseline timepoint of Visit 1, we collect whole blood for apolipoprotein E4 (*APOE4*) genotyping, which is immediately frozen in polypropylene cryovials at -80C. Whole blood is also analyzed at baseline for HbA1c using the DCA Vantage Analyzer (Siemens, Tarrytown, NY). Additionally, 2 mL of whole blood is collected in a 2 mL lithium heparin tube for lipid analysis using the Cholestech LDX Lipid Profile Test Cassette (Abbott, San Diego, CA). Finally, we collect 10 mL of blood into EDTA plasma tubes at all timepoints of the OGTT. At the baseline timepoint, we generate both platelet-rich plasma (PRP) and platelet-poor plasma (PPP). For subsequent time points at 30, 60, and 120 min, only PRP is generated. PRP is prepared by centrifuging whole blood at 1500 x g for 10 min at 4 °C, followed by careful removal of plasma. PPP requires an additional centrifugation step at 1700 x g for 15 min at 4 °C. Plasma will be frozen and analyzed at the end of the study for various biomarkers using immunoassays for the specific proteins of interest: TNF, IL-6: Cytokine 4-Plex A (C4PA) Advantage PLUS, Neuro 2 Plex B assay (N2PB) on the Simoa HD-X (Quanterix, Billerica, MA) and phosphorylated tau 217 and amyloid beta 42 on the Lumipulse G1200 (Fujirebio). As an exploratory outcome, plasma heat shock protein 70 (HSP70) will be quantified to assess heat therapy–related activation of the heat shock response.

### Statistical analysis plan and power

3.7

We will conduct an analysis to assess changes in blood glucose regulation in response to 10 weeks of HT of either thermoneutral or hot water immersion. The primary outcome measures are change in HbA1c and ISI from pre- to post-heat therapy. A secondary outcome measure is change in global FDG SUVR from the pre- to post-intervention.

The primary statistical analyses will contrast change scores in HbA1c and ISI following 10 weeks of HT between the temperature groups (warm vs. hot) using two-sample paired t-tests. We will conduct residual analyses to assess the appropriateness of this methodology to evaluate assumptions of common variance, normally distributed errors, etc. In the event any of the measures do not conform to these foundational assumptions, the nonparametric analogs will be used instead, such as the Wilcoxon rank sum test of the within-subject baseline vs. post-treatment stimulated change score (difference) measures. These measures will follow the intent-to-treat principals. Though a randomized design, we will also construct exploratory analyses that incorporate other adjustments using ordinary least squares (OLS) regression on the change scores as the outcomes, also with residual analysis and modified approach if indicated. This will allow for model adjustment to further examine these relationships.

One further relationship will involve combining both HT groups in a single model. Finally, we will model change score outcomes as functions of the various other change score measures. This approach will enable us to observe how changes in HbA1c and ISI are driven by heat therapy-influenced changes in other factors, such as circulating biomarkers. We will conduct similar residual analyses appropriate to the regression models utilized to ensure appropriate inferences are drawn. While descriptive and exploratory in nature, we anticipate that this approach will illuminate and/or confirm pre-conceived metabolic processes that are related to the HT response, and that it will help identify likely reasons for prior HT trial successes and failures through mechanistic discovery.

For Aim 1, we calculated the sample sizes needed for achieving different levels of power (80–95%), with respect to different effect sizes. The effect size here is defined as pre- and post- intervention change in ISI. The effect size 0.42 was given from Ely et al., who tested a similar heat therapy intervention (3x per day for 10 weeks) in a younger, obese population (3). Given the different patient population, use of this effect size could be a potential limitation. Effect sizes 0.24 and 0.15 were computed by subtracting 1 and 1.5 times of the pooled standard error (SE) of 0.18 (see Table 1 in Ely et al.) from 0.42. The effect size 0.1 is very conservative and corresponds to subtracting 1.8 times the SE from 0.42. That effect size will require 51 samples to achieve 80% of power. We expect to potentially have 10% attrition and an extra 5% missing data in each group. With these considerations, our planned sample size of 30 per group would provide more than 85% power to detect change in our primary Aim 1 outcome, even withstanding possible attrition and missing data.

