### Trial design

3.1

FIGHT-AD is a two-arm, prospectively enrolling randomized controlled trial that compares the effects of thrice weekly HT in water immersion for 10 consecutive weeks on glucose metabolism in warm (*n* = 30) and hot (*n* = 30) water. Participants will complete telephone cognitive testing and clinical evaluation to screen for any cognitive impairment. After screening, informed consent will be obtained and participants will be enrolled into the study. Cognitively healthy older adults who meet the criteria for metabolic syndrome will be enrolled and complete (1) a fasting blood draw; (2) an Oral glucose tolerance test (OGTT); and (3) CGM, MRI and an FGD-PET scan. Assessments will be repeated following 10 weeks of HT. Participants will undergo 30 sessions of HT in 40.5 °C water or 36 °C water to assess the effect of temperature on changes in blood and brain glucose metabolism. The flow of the study is illustrated in Figure 1.

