Following successful completion of baseline assessments, participants are randomized to receive treatment in hot or warm water temperature group. An allocation table was created by the unblinded study statistician working with the study team. Randomization is performed using the REDCap randomization module (23). Individuals are randomized 1:1 to intervention group according to the allocation table accounting for sex and age to ensure approximately equal representation among HT groups. At each subsequent study visit, participants complete 45 min of HT. Assessment of DEXA, GTT, FDG-PET, CGM and MRI are repeated after 10 weeks HT. Study staff who oversee therapy sessions will be unblinded to study group. All outcome assessors (psychometricians, nursing staff, neuroimaging technicians, etc) are blinded to participant intervention group. Study data is stored using REDCap software in a secure study database.

#### Visits 1 & 4

3.3.1

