## Anticipated results

4

HT has emerged as a promising, non-pharmacologic intervention that is being investigated as an intervention to reduce the risk of AD. We are focusing on its effects on blood and brain glucose metabolism, and other factors such as proteostasis, inflammation, and vascular function —factors linked to AD neuropathology. Our recent pilot study provided evidence for safety and feasibility of a 4-week heat therapy intervention protocol in cognitively healthy older adult populations (24). The 10-week FIGHT-AD study will add to our understanding of the impact of HT on whole body metabolic function and brain health.

For the proposed study, individuals will undergo up to 30 sessions of hot (40.5 °C, *n* = 30) or warm (36 °C, *n* = 30) water immersion to assess the effect of temperature on the changes in blood and brain glucose metabolism (pre to post). We hypothesize that 10 weeks of HT will lower HbA1c values and improve insulin sensitivity index outcomes. Additionally, we hypothesize that individuals will improve (increase) global cerebral glucose metabolism following 10 weeks of HT. We will also explore effects on other outcome measures such as blood pressure, blood AD biomarkers, and brain blood flow.

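### The named primary test, a paired t-test between the warm and hot arms, does not apply to two independently randomised groups and contradicts the rest of its own paragraph

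*Protocol article*

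**What the plan says.** Section 3.7 (Statistical analysis plan and power) makes change in HbA1c and change in ISI the primary outcomes and contrasts them "between the temperature groups (warm vs. hot) using two-sample paired t-tests". Residual analyses follow "to evaluate assumptions of common variance, normally distributed errors, etc". If the assumptions fail, the plan turns to nonparametric analogs, for example "the Wilcoxon rank sum test of the within-subject baseline vs. post-treatment stimulated change score (difference) measures". It then adds exploratory least-squares regression on the change scores.

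Section 3.1 (Trial design) states the design: "FIGHT-AD is a two-arm, prospectively enrolling randomized controlled trial". Section 3.3 (Procedures) gives the allocation: "Individuals are randomized 1:1 to intervention group according to the allocation table accounting for sex and age". The stated purpose of that adjustment is a roughly even mix of sex and age across the arms. It does not create matched pairs.

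Two other places use pre-to-post language. Section 4 (Anticipated results) says "We hypothesize that 10 weeks of HT will lower HbA1c values and improve insulin sensitivity index outcomes", and the power paragraph of section 3.7 says "The effect size here is defined as pre- and post- intervention change in ISI". Section 3.7 also applies the term HT to both the thermoneutral and the hot immersion.

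**The concern.** A paired t-test needs a natural link between each observation in one sample and one in the other. The only link in this design is between a person's own two visits, and taking the change score has already used it. The remaining comparison is between different people in different arms, for which a paired test is not defined.

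An analyst who followed the words would have to do one of two things:

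- **Pair unrelated people across arms.** The result then depends on the order of the rows, and anyone without a partner is lost.
- **Apply the pairing to the two visits within each arm.** That is a pre/post test. It credits to heat any time trend, regression to the mean or immersion effect, and section 3.4.3 includes the 36 °C arm because immersion itself may affect physiology.

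This is the only test named for both primary outcomes, and nothing else in the article corrects it. Left as it stands, it leaves room to choose between analyses after the data are seen.

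**Working it through.** **1. Is there any pairing across arms?** Sections 3.1 and 3.3 describe 1:1 individual randomisation with sex and age taken into account in the allocation table. No matched sets are described, so the answer is no.

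**2. What does the rest of the paragraph imply?**

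| Element of section 3.7 | Belongs to |
|---|---|
| Change contrasted between warm and hot | independent samples |
| Common-variance check | independent samples |
| Wilcoxon rank sum fallback | independent samples (the analog of a paired t-test is the signed rank test) |
| Least-squares regression on change scores | independent observations |
| The word *paired* | dependent samples |

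One word stands against four elements.

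**3. Does the plan's own sample-size figure settle it?** The plan says an effect of 0.1 needs 51 for 80% power, without saying whether that is per arm or in total. It gives a pooled SE of 0.18. Alpha is not stated, so I assume 0.05 two-sided. I use 0.18 as an SD only because that reproduces the figure.

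- Independent samples: n per arm = 2 × 0.18² × (1.960 + 0.842)² / 0.1² = 50.9, rounded up to **51**. The exact t version gives 51.8, so 52.
- Paired, SD of differences 0.18: n = 0.18² × (1.960 + 0.842)² / 0.1² = 25.4, rounded up to **26**. The t version gives 27.4, so 28.
- Paired, SD of differences 0.18 × √2 (pre and post uncorrelated): also **51**.

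The 51 fits an independent-samples calculation but does not prove one.

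**4. Arbitrary pairing, run literally.** The plan allows 10% attrition plus 5% missing data, so 30 × 0.85 = 25.5, or about 26 per arm. Simulation with 20,000 trials, 26 per arm, normal data, two-sided 0.05:

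| | Independent test | Arbitrary pairs | Verdict flips on re-pairing |
|---|---|---|---|
| No effect (type I error) | 5.1% | 5.2% | 2.8% |
| Effect 0.15/0.18 = 0.83 SD (power) | 84.2% | 82.6% | 6.2% |

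With 30 per arm, degrees of freedom fall from 58 to 29 and the critical t rises from 2.00 to 2.05. If losses leave the arms unequal, the surplus in the larger arm has to be dropped.

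**5. Within-arm pre/post reading.** Assume both arms change by the same amount, so heat has no effect. The size of the common change is my assumption, since the article gives none. With 26 per arm, the hot arm's one-sample test on change is significant as follows:

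| Common change (SD of change) | Hot arm significant |
|---|---|
| 0.2 | 17% |
| 0.3 | 32% |
| 0.5 | 69% |

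These rates apply only if someone takes a within-arm test as the trial result.

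**The case against.** The strongest reply is that this is a slip of one word. The sentence contrasts change scores between the temperature groups, which a within-arm test cannot do. The variance check, the rank sum fallback and the regression all point to an unpaired test, with *paired* describing how each person's change was formed. The introduction, section 3.1 and section 4 all say the aim is to assess the effect of temperature, and section 3.4.3 explains why the control arm exists. Most of this stands, and I take an independent-samples test to be the likely intent.

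Three stronger readings are therefore not supported:

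- **A reader might infer that the primary analysis discards the control arm.** The sentence itself names a warm-versus-hot contrast. The within-arm reading is a secondary risk, created by the loose use of HT for both arms, hypotheses without a comparator, and an effect size defined as pre/post change.
- **A reader might infer that the test inflates false positives.** Arbitrary pairing does not. Type I error stays near 5% and the power loss is small. The harm is a result that is not uniquely defined.
- **A reader might infer that allocation by sex and age supplies the pairs.** Balance in an allocation table does not match individuals.

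The objection does not repair the text. A published primary analysis still names a test that does not apply, and the reader has to infer the intended one.

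**Conclusion.** The point holds as an error in the named primary test, probably one of wording. As written, the test does not fit two independent arms and conflicts with the checks and fallback in the same paragraph.

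The direct statistical cost of a literal reading is modest: 1 to 2 points of power, a verdict that depends on row order in about 3% (null) to 6% (alternative) of trials, and possible loss of unpaired participants. The larger potential harm, 17% to 69% spurious significance in the hot arm, depends both on a within-arm reading that the primary sentence does not support and on an assumed common change of 0.2 to 0.5 SD. All simulation figures assume normal data, 26 per arm and two-sided 0.05.

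**What to change.** In section 3.7, and in the full protocol and analysis plan if they carry the same words:

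1. Replace the paired test with an independent two-sample t-test on within-person change scores, hot minus warm, for HbA1c and ISI.
2. Keep the Wilcoxon rank sum test on change scores as its nonparametric analog, worded as a comparison between arms.
3. State the primary hypotheses as hot-minus-warm differences in change, and say that within-arm pre/post tests are descriptive only.

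Whether to adjust for baseline or allow unequal variances is a separate choice that this correction does not depend on.

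The cost is a wording amendment, with no new data or procedures. On the plan's own inputs the sample-size figure is essentially unchanged, at 51 per arm (52 by exact t) for an effect of 0.1.

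### The primary test compares change scores without adjusting for baseline, sex or age; it is unbiased but gives up a modest amount of precision

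*Protocol article*

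**What the plan says.** Section 3.7 (Statistical analysis plan and power) says the primary analyses will "contrast change scores in HbA1c and ISI following 10 weeks of HT between the temperature groups (warm vs. hot) using two-sample paired t-tests". I read this as a two-sample t-test on within-person changes; the wording of the test is contradictory, but that is a separate matter. If assumptions fail, the fallback is the "Wilcoxon rank sum test of the within-subject baseline vs. post-treatment stimulated change score (difference) measures". Neither test contains a covariate.

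Adjustment appears only as a further step: "Though a randomized design, we will also construct exploratory analyses that incorporate other adjustments using ordinary least squares (OLS) regression on the change scores". The covariates are not named.

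Section 3.3 (Procedures) says "Individuals are randomized 1:1 to intervention group" and that this is done "according to the allocation table accounting for sex and age to ensure approximately equal representation among HT groups". It also places randomisation after the baseline assessments. Those include the oral glucose tolerance test (sections 3.1 and 3.3.1.2) and HbA1c (section 3.6), so baseline values of both primary outcomes should exist for essentially everyone randomised.

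**The concern.** The trial has 60 participants, so precision is scarce. Under section 3.2 the sample can include people with type 2 diabetes on non-insulin drugs, people with prediabetes, and people with neither who have two of three other risk factors. Baseline HbA1c and ISI will differ between people, and the two arms can differ at baseline by chance.

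A change score subtracts the whole baseline value, which amounts to fixing the regression slope on baseline at 1. When the correlation between the two measurements is below 1 and their variances are similar, that over-corrects. An arm that starts higher by chance will then tend to show a larger fall. Estimating the slope from the data removes this.

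The allocation factors raise a related point. If randomisation balances sex and age and these predict change, a test that omits them uses a standard error that is too large. Because the article fixes the unadjusted test as primary and labels adjustment exploratory, an SAP that follows it could not make the adjusted model primary.

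**Working it through.** **Inputs from section 3.7.** Effects on ISI change of 0.42, 0.24, 0.15 and 0.1; spread 0.18 (called a pooled standard error); 51 needed for effect 0.1 at 80% power; 30 per group; 10% attrition plus 5% missing data; power of more than 85%.

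**Assumptions, not in the documents.** Two-sided alpha 0.05; pre/post correlation r from 0.5 to 0.9; equal variances before and after treatment; sex and age explaining 5% to 20% of the variance of change.

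**1. The plan's own figures.** With 0.18 as the SD of change, n per group = 2 × (1.96 + 0.842)² × 0.18² / 0.1² = 50.9, so 51. This matches the article exactly.

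After 15% loss, 30 × 0.85 = 25.5 per group remain. At effect 0.15, the standard error is 0.18 × √(2/25.5) = 0.0504, the ratio is 0.15/0.0504 = 2.976, and power is Φ(2.976 − 1.96) = 84.5%. That is close to the stated figure. At effect 0.24 power exceeds 99%, and at effect 0.1 it is 51.0%. These are normal approximations; the t distribution gives 83.1% in place of 84.5%.

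**2. Effect of baseline adjustment.** With outcome variance σ², the variance of a change is 2σ²(1 − r) and the residual variance after adjustment is σ²(1 − r²). The ratio is (1 − r²) / [2(1 − r)] = (1 + r)/2. Power with 25.5 per group uses SD = 0.18 × √[(1 + r)/2]:

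| Analysis | Variance ratio | Power, effect 0.15 | Power, effect 0.1 |
|---|---|---|---|
| Change score | 1.00 | 84.5% | 51.0% |
| Adjusted, r = 0.5 | 0.75 | 93.0% | 63.0% |
| Adjusted, r = 0.7 | 0.85 | 89.8% | 57.6% |
| Adjusted, r = 0.8 | 0.90 | 88.0% | 55.2% |
| Adjusted, r = 0.9 | 0.95 | 86.3% | 53.0% |

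Estimating the baseline slope in about 51 people inflates the variance by roughly 1 + 1/(51 − 4) = 1.02. At r = 0.9 the net ratio is therefore about 0.95 × 1.02 = 0.97.

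**3. Chance imbalance.** With 30 per arm the standard error of the baseline difference is √(2/30) = 0.258 SD. A difference beyond 0.25 SD (z = 0.97) occurs in about 33% of trials, and one beyond 0.5 SD (z = 1.94) in about 5%.

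A fraction (1 − r) of the imbalance carries into the change-score contrast, whose own standard error is √[2(1 − r)] × 0.258 SD. A one-standard-error imbalance has this effect:

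- r = 0.5: a shift of 0.129 SD against a standard error of 0.258 SD, a ratio of 0.50.
- r = 0.8: a shift of 0.052 SD against 0.163 SD, a ratio of 0.32.

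The squared ratio is (1 − r)/2, the same variance share as in step 2. This is the same loss seen from within one trial, so it should not be counted twice.

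**4. Allocation factors.** In 20,000 simulated trials per setting, with four balanced sex-by-age strata and no treatment effect, the unadjusted t-test rejected in about 4.5%, 3.7% and 2.7% of trials when the strata explained 5%, 10% and 20% of the variance of change. The stratum-adjusted model rejected in about 5%.

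**The case against.** The planned contrast is valid. Randomisation makes it unbiased, its type I error is not inflated, and omitting the allocation factors errs on the cautious side. This stands in full.

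The gain may also be small. Wide, stable differences between people raise r, and the sample is mixed, on stable medication and followed for only 10 weeks. A high r is plausible, at least for HbA1c, and the saving is then nearer 5% to 10% than 25%. This stands too, and it is why the range runs to 0.9. Likewise, sex and age may explain little of a change score, and the article promises only approximate balance, so the figures in step 4 may overstate the effect.

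Regressing the change on arm and baseline gives the same arm estimate as regressing the post value. If baseline is among the unnamed exploratory adjustments, the better estimator is already planned. It would still not be the primary one.

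A reader might draw three stronger conclusions that the documents do not support:

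- **That baseline is ignored.** A change score subtracts it. What is missing is adjustment for it.
- **That participants without a post value are dropped, so intention to treat is not delivered.** Section 3.7 says "These measures will follow the intent-to-treat principals" and allows for 15% loss in the sample size. It states no exclusion rule, and a condensed article commonly leaves missing-data handling to the SAP.
- **That a baseline imbalance of 0.5 SD is ordinary.** It would be exceeded in about one trial in twenty.

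**Conclusion.** The point holds as one of efficiency and of protection against chance imbalance. It corrects no bias and no inflated error rate. The article fixes an unadjusted primary test although baseline is measured before randomisation and allocation accounts for sex and age.

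Baseline adjustment would save 5% to 25% of the variance for r from 0.9 to 0.5. That is about 2 to 8 percentage points of power at effect 0.15, and about 2 to 12 at effect 0.1. It would lift the 84.5% recomputed at effect 0.15 above the 85% that the plan states, though at r = 0.9 only just.

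These results rest on equal variances, an assumed r, an assumed two-sided alpha of 0.05, and 0.18 being used as an SD, which is the use that reproduces the 51. They concern ISI, the outcome on which the power text is based. The loss from omitting sex and age depends on an assumed share of the variance of change and may be slight.

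**What to change.** For each primary outcome, make the primary analysis a regression of the post-treatment value on arm, baseline value of that outcome, sex and age. Using the change as the response, with the same covariates, gives the same arm estimate. State that age enters in the form used in the allocation table or as a continuous term. Keep the change-score t-test and the rank-sum test as named sensitivity analyses, and reserve the exploratory label for models with further covariates.

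The cost is a change of wording in the SAP and about three degrees of freedom if age is a single term. No additional data or participants are needed.

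### The power paragraph labels 0.18 a standard error, but its 51 arises only if 0.18 is a standard deviation, so the claimed power of over 85% is unsupported

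*Protocol article*

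**What the plan says.** Section 3.7 of the protocol article sizes the trial on ISI, one of the two primary outcomes. The effect is a raw change, not a standardised one: "The effect size here is defined as pre- and post- intervention change in ISI". The starting value, 0.42, comes from an earlier heat-therapy study in a younger, obese population. Smaller effects are obtained by subtraction: "Effect sizes 0.24 and 0.15 were computed by subtracting 1 and 1.5 times of the pooled standard error (SE) of 0.18". A fourth follows: "The effect size 0.1 is very conservative and corresponds to subtracting 1.8 times the SE from 0.42". For that fourth effect the article states: "That effect size will require 51 samples to achieve 80% of power". On losses it says: "We expect to potentially have 10% attrition and an extra 5% missing data in each group". It concludes that "our planned sample size of 30 per group would provide more than 85% power to detect change in our primary Aim 1 outcome", after allowing for those losses.

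The section gives no SD, no alpha or sidedness, and no size for the source study. It does not say which of the four effects the power figure refers to. The primary analysis, described earlier in the same section, contrasts change scores between the hot and warm groups.

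**The concern.** A standard error of a mean is the SD divided by the square root of the number of subjects, so one value cannot serve as both. The article uses 0.18 as an SE when it shrinks the effect. The sample size that follows needs 0.18 to be the SD.

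This paragraph is the only power justification for ISI. If ISI turns out null, readers will set that result against a claim of more than 85% power and may take it as good evidence of no effect. If the true power is much lower, that inference fails.

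**Working it through.** **Inputs.** All from section 3.7: effects 0.42, 0.24, 0.15 and 0.1 (0.42 − 1.8 × 0.18 = 0.096); spread 0.18; 30 per arm; losses of 10% + 5%, so 30 × 0.85 = 25.5 per arm. Assumed: two-sided 5%, which is the level that reproduces 51.

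**Reproducing the 51.** Two arms, normal approximation, SD = 0.18:

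n per arm = 2 × (1.960 + 0.842)² × (0.18/0.10)² = 50.9, so 51.

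A paired total with an SD of the difference of 0.18 × √2 = 0.255 gives the same figure: (1.960 + 0.842)² × (0.255/0.10)² = 50.9. Both routes use 0.18 as an SD. The alternatives tried do not give 51:
- one-sided 5%: 41 per arm
- one-sample test with SD 0.18: about 27
- 0.1 read as a standardised effect: about 1,570 per arm, or 787 pairs

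**Power if 0.18 is an SE.** The source group size m is not given; 6 to 20 is assumed. Two-sided 5%, 25.5 per arm, noncentral t.

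| What 0.18 is | m | SD of change | 0.42 | 0.24 | 0.15 | 0.1 |
|---|---|---|---|---|---|---|
| SE of one group's mean change, SD = 0.18√m | 6 | 0.44 | 92% | 48% | 22% | 13% |
| | 10 | 0.57 | 73% | 32% | 15% | 9% |
| | 20 | 0.80 | 45% | 18% | 10% | 7% |
| SE of a between-arm difference, SD = 0.18√(m/2) | 6 | 0.31 | >99% | 77% | 39% | 20% |
| | 10 | 0.40 | 96% | 55% | 26% | 14% |
| | 20 | 0.57 | 73% | 32% | 15% | 9% |

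At 0.42, 85% power needs an SD of at most about 0.50. Under the first reading that means (0.50/0.18)² = 7.7, so m of 7 or fewer. Under the second, m may be up to about 14.

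**A third reading.** If 0.18 is the SE of a pre or post level, the SD of change is 0.18√m × √(2(1 − ρ)), with ρ the unstated pre-post correlation. At ρ = 0.5 this equals the first reading. At ρ = 0.7 and m = 10 the SD is 0.44, and power (normal approximation) is about 92% at 0.42 and 23% at 0.15.

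**Power if 0.18 really is the SD.** With 25.5 per arm, the between-arm contrast has about 83% power at 0.15 and 49% at 0.1. For that contrast the 51 is a number per arm, above the planned 30.

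**What 30 per arm can detect.** With 25 to 26 per arm, power is 80% for a difference of about 0.80 SD and 85% for about 0.86 SD. For an SD of 0.44 to 0.80, the 80% figure is 0.80 × 0.44 = 0.35 to 0.80 × 0.80 = 0.64 ISI units.

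**The case against.** Four objections deserve weight.

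1. *The design may still have the stated power.* A reader might infer that 30 per arm cannot deliver 85%. The document does not support that. It never says which effect the 85% belongs to, and at the full 0.42 power can exceed 85% when the source groups were small, when 0.18 is the SE of a between-arm difference, or when pre-post correlation is high. This objection stands and limits the conclusion at 0.42.

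2. *The 85% cannot be traced to one effect.* It is tempting to say it was computed at 0.15 with SD 0.18, since 2 × (1.960 + 1.036)² × (0.18/0.15)² = 25.9, or 26 per arm. But that means picking one effect of four and rounding 25.5 up, and a t-test at 25 to 26 per arm gives 82% to 84%. Sixty pooled pairs at 0.1, with an SD of the difference of 0.255, also give about 85%. The match is only suggestive.

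3. *The size of the understatement is not fixed.* A reader might infer that the required n is too small by a factor equal to the source group size. That holds only if 0.18 is the SE of one group's mean change. For a between-arm difference the factor is m/2, and for a level it also depends on ρ.

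4. *SE may be a slip for SD.* In that case the 51 stands as arithmetic. Nothing in the article supports this reading, though the source table could. It would not settle the matter: power at 0.1 for the planned contrast would still be about 49%. Nor does reading 51 as a pooled total (60 × 0.85 = 51) help, because a pooled pre-post change is not the primary comparison.

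The article does concede that borrowing the effect is a limitation, but it means the difference in population, not the spread.

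**Conclusion.** The power statement is wrong as written. The spread is labelled and used as an SE, the 51 requires it to be an SD, and the claim of over 85% therefore lacks support. This much follows from section 3.7 itself, with only two-sided 5% assumed.

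The loss of power depends on what 0.18 is and on a source group size that the document does not give. Under either of the two SE readings in the table, with m from 6 to 20, power falls below 85% at every reduced effect: 77% to 18% at 0.24, 39% to 10% at 0.15 and 20% to 7% at 0.1. At 0.42 it runs from above 99% down to 45%, so the shortfall there is conditional. If 0.18 is a mislabelled SD, the smallest effect listed is still underpowered for the between-arm contrast.

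**What to change.** Keep 30 per arm and rewrite the power paragraph:
- Check the source table and state whether 0.18 is an SD, the SE of a mean change, the SE of a difference or the SE of a level, and give the source group size.
- State the SD of the ISI change score, the target between-arm difference, alpha and sidedness.
- Recompute power for the between-arm contrast with about 25 per arm, and name the effect that it refers to.
- Replace the 51 and the claim of over 85% with the recomputed figures, or with the detectable difference (about 0.80 SD at 80% power and 0.86 SD at 85%).

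The cost is one paragraph. No participants are added, and no outcome or analysis changes. The stated power may become less favourable.

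### The claim of more than 85% power after attrition names no effect size and cannot hold at effect 0.1, where the plan's own figures give 80% at most and possibly about 50%

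*Protocol article*

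**What the plan says.** All of this is in the protocol article, section 3.7 (Statistical analysis plan and power). The effect size is a change in the insulin sensitivity index (ISI): "The effect size here is defined as pre- and post- intervention change in ISI". Four values are listed. The largest, 0.42, comes from an earlier heat therapy study in younger obese adults. The next two are derived from it: "Effect sizes 0.24 and 0.15 were computed by subtracting 1 and 1.5 times of the pooled standard error (SE) of 0.18". The smallest follows: "The effect size 0.1 is very conservative and corresponds to subtracting 1.8 times the SE from 0.42".

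One sample size is given, and it belongs to the smallest effect: "That effect size will require 51 samples to achieve 80% of power". The text does not say whether 51 is a total or a number per group. Losses come next: "We expect to potentially have 10% attrition and an extra 5% missing data in each group". The conclusion is that "our planned sample size of 30 per group would provide more than 85% power to detect change in our primary Aim 1 outcome", and that this is so "even withstanding possible attrition and missing data". The concluding sentence names no effect size, and the section states neither alpha nor a standard deviation.

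**The concern.** The section shows one pairing of sample size and power: effect 0.1, 51 samples, 80%. The loss allowance and the claim of more than 85% follow directly, so a reader will naturally apply the 85% to effect 0.1. With 60 enrolled and 15% lost, 51 remain in total, or 25–26 per group. That is the number the plan ties to 80% if 51 is a total, and half of what it requires if 51 is per group.

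This paragraph is the article's only justification for 30 per group. A null ISI result would be read against an assurance of more than 85% power that the design does not give at the smallest effect the plan presents.

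**Working it through.** **Inputs from section 3.7.** Effects 0.42, 0.24, 0.15 and 0.1; spread 0.18 (called a pooled standard error); 51 samples for 80% power at 0.1; 30 per group; 10% attrition plus 5% missing data.

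**Assumptions.** Two-sided alpha 0.05, equal groups, and 0.18 used as the SD of the change score. None of these three is stated in the power paragraph; 1:1 allocation is stated in section 3.3.

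**Effect sizes.** 0.42 − 0.18 = 0.24; 0.42 − 1.5 × 0.18 = 0.15; 0.42 − 1.8 × 0.18 = 0.096, about 0.1. These agree with the text.

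**Reproducing 51.** The two-sample formula under the normal approximation gives n per group = 2 × (1.960 + 0.8416)² × (0.18/0.10)² = 50.9, so 51 per group. A one-sided 5% test would give 41, so two-sided fits. Because the effect is defined as a pre–post change, another route is possible. A one-sample calculation with SD 0.18 × √2 also gives 50.9, this time as a single sample. The arithmetic therefore does not settle what 51 counts.

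**Losses.** 60 × 0.85 = 51.0 and 30 × 0.85 = 25.5. Applied one after the other, 30 × 0.90 × 0.95 = 25.65, or 51.3 in total.

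**Reading A: 51 is a total.** Power with m evaluable = Φ(2.8016 × √(m/51) − 1.96).
- Effect 0.1, m = 60, no loss: 86.0%.
- Effect 0.1, m = 51, after loss: 80.0% (80.2% at 51.3).
- Effect 0.15, m = 51: Φ(1.5 × 2.8016 − 1.96) = 98.8%.
- Effects 0.24 and 0.42: above 99%.

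With a one-sided test, effect 0.1 gives 85.4% before loss and still 80% after.

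**Reading B: 51 is per group.** Power = Φ(δ / (0.18 × √(2/n)) − 1.96), with the noncentral t value beside it.

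| Effect | 30 per group: normal / t | 26 per group: normal / t | 25 per group: normal / t |
|---|---|---|---|
| 0.10 | 57.6% / 56.2% | 51.7% / 50.2% | 50.2% / 48.6% |
| 0.15 | 89.8% / 88.8% | 85.2% / 83.8% | 83.8% / 82.3% |
| 0.24 | 99.9% / 99.9% | 99.8% / 99.7% | 99.7% / 99.6% |

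At 0.42 power is about 100% throughout. On this reading 30 per group is below 51 before any loss.

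**The case against.** The strongest reply is that the 51 and the 85% need not refer to the same effect. The 51 is tied to 0.1, which the plan calls very conservative, while the 85% sentence names no effect and the section says that power of 80–95% was examined across several.

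There is also a plausible route to the claim at 0.15. For 85% power, 2 × (1.960 + 1.0364)² × (0.18/0.15)² = 25.9, so 26 per group; power at 26 is 85.2%; and 26 × 1.15 = 29.9, so 30. That yields both the planned number and the stated power after losses.

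Much of this stands. A reader might infer that 85% is a no-attrition figure on every reading, or that the sentence flatly contradicts the paragraph. The document supports neither. After losses, power exceeds 99% at 0.24 and 0.42, and at 0.15 it is 98.8% if 51 is a total.

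The 0.15 route is nevertheless thin. It multiplies by 1.15 where allowing for a 15% loss means dividing by 0.85 (26 / 0.85 = 30.6, above 30). It rounds 25.5 up in both groups; at 25.5 the normal approximation gives 84.5%. It also uses a normal approximation, whereas the section plans t-tests. In fairness, the normal approximation is the method that reproduces 51, so the gap at 0.15 is a matter of rounding and method. None of this rescues effect 0.1.

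**Conclusion.** The concern holds in a limited form. The power statement is unqualified, and it is untrue at effect 0.1, the only effect for which the section gives a sample size. Power there after the plan's own losses is 80% if 51 is a total and about 49–52% if 51 is per group. At 0.15 the claim is borderline on the per-group reading (82–84% by t-test, 84–85% by normal approximation, at 25–26 per group) and holds on the total reading. At 0.24 and 0.42 it holds.

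The 80% at effect 0.1 on the total reading follows from the plan's own pairing and needs no SD. The other figures rest on two-sided 5%, and those on the per-group reading also use 0.18 as an SD. Since the plan calls 0.18 a standard error, they are conditional; if the SD is larger, power is lower. That the trial is too small overall does not follow from this point.

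**What to change.** - State whether 51 is a total or a number per group.
- Replace the blanket sentence with power at 25–26 evaluable per group for each of the four effect sizes, naming the SD, alpha and test behind the figures.
- Say what 0.18 is. Fix this and the meaning of 51 before printing any replacement numbers, because the figures depend on both.
- Confine the claim of more than 85% after losses to the effect sizes where it holds. State that at 0.1 power is at most 80% after losses, or about 50% if 51 is per group.

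The cost is a less favourable power statement. Enrolment, conduct and the planned analysis do not change.
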